### Status and timeline of the study

Recruitment has started in August 2021 and data collection has started at the end of September 2021. The first version of this study protocol has been submitted before start of data collection. All recommendations from the reviewers’ first reviews were considered. Data collection will last until the recruitment goal is fulfilled. The actual duration will depend on the development of the Covid-19 pandemic but is intended to last about one year. Data analysis will start after all data will have been collected. Preliminary analyses are not planned.

### Experimental conditions

An overview about all experimental conditions is provided in Table 1. Condition 1 will be a passive control condition, in which participants will watch a non-stressful video. Condition 2 will be an active control condition, in which participants will conduct a digital single-task, which is the primary task in the other (dual- and multitasking as well as the interruption) experimental conditions. In conditions 3 to 5, participants will conduct the primary task either in combination with a parallel secondary task or will be interrupted by a secondary task. Participants who are assigned to condition 6 will be engaged in multitasking, which will include three tasks, the primary task as well as a digital and a non-digital parallel task. All conditions are visualized in Fig 1 and are summarized in Table 1.

### Tasks

#### Digital primary task

A computerized continuous-performance task [CPT; 58,59] will be the primary task for the single-task as well as the dual-task and multitasking conditions (conditions 2–6 in Fig 1). The CPT is a measure for sustained attention [60]. We will use an AX-CPT variant [e.g., 61], i.e. that the target is the letter ‘X’ occurring after an ‘A’. In our version (Fig 2), the letters A, B, X, and Y will be presented, and a response button should be pressed after every second letter, i.e., after a pair of letters. The cue letter is ‘A’ and the target letter is ‘X’, i.e., that one response button should be pressed after each A-X pair. In all other cases (after A-Y, B-X, B-Y pairs), the other response button should be pressed (Fig 2). In our AX-CPT version, the letter presentation time is 2,000 ms and the inter-stimulus interval is 3,500 ms. The probability of an A-X pair is 0.50 and 0.17 for the other pairs.

**Fig 2 pone.0263785.g002:**
[figure not shown]
AX-CPT. In our version of the AX-CPT, the target pair will be A-X. A-Y, B-X, as well as B-Y pairs will be non-targets. This task will be used as the digital single-task and will be the primary task in the dual- and multitasking conditions.

#### Digital secondary task

As a digital secondary task, questions and five answer possibilities, of which one is correct, will be presented to the participants. The answer possibilities will be assigned to five answer buttons, and the instruction is that the correct answer should be chosen as fast as possible. As questions, items from the *Intelligenz-Struktur-Test 2000R* [IST- 2000R; 62,63] will be used and will be presented in a randomized order. The following sub-tasks will be chosen: sentence addition (*Satzergänzung*), analogies (*Analogien*), and figure selection (*Figurenauswahl*). In condition 3 (digital interruptions), the primary task will be interrupted by questions from the IST 2000R, which will appear on the same monitor. The primary task will stop and will be overlayed by the secondary one during the presentation of the secondary task and will automatically continue after a response is given by the participant. In condition 4 (dual-task, parallel condition), participants will have to perform the IST 2000R on a separate computer screen parallel to the primary task. The participants will be instructed that both tasks are equally relevant, i.e., that none of the tasks should be prioritized, and that both tasks should be performed as accurately as possible.

#### Non-digital secondary task

As non-digital secondary task, participants will have to conduct a verbal-fluency task [VFT; e.g., 50,64]. The instruction, which will be verbally given by the experimenter, is to name as many words as possible that belong to a given category or which begin with a given letter. The time per category/letter will be 2 minutes, and time between two rounds will be 1 minute. Each participant will conduct six rounds with the same categories/letters in a randomized order. This secondary task will be conducted in parallel to the primary task (i.e., the AX-CPT; condition 5 in Fig 1). The experimenter will be in the same room as the participant to introduce a social-evaluative component. As for the digital parallel task, participants will be instructed that both tasks are equally relevant, i.e., that none of the tasks should be prioritized, and that both tasks should be performed as accurately as possible.

In the multitasking condition (condition 6 in Fig 1), all three tasks (AX-CPT, the digital parallel task, as well as the VFT) should be performed in parallel and, again, none of the tasks should be prioritized.

#### Passive control condition

The (digital) passive control condition will be to watch a non-stressful documentary video (condition 1 in Fig 1). The content of the video is landscapes and animals. These videos have been successfully used in previous studies and evaluated as being non-arousing [65,66].

### Biological and physiological outcome measures

Main outcomes will be measures for physiological stress responses, which will be assessed via saliva and capillary blood samples as well as by means of electrocardiogram (ECG) recordings. An overview is provided in Table 2. As measures for SNS re-activity, salivary alpha-amylase [67] as well as the participants’ heart rate will be used. PNS re-activity will be assessed from heart rate variability (HRV) measures [e.g., root mean square of successive differences of consecutive R-R intervals (RMSSD); 68]. Activity of the HPA axis will be assessed via salivary cortisol measurements, which will be collected by means of *Salivettes* (Sarstedt, Nümbrecht, Germany). IL-6 and CRP will be assessed from capillary blood samples, which will be measured in Dried Blood Spots [69,70], which is an established procedure in our group [e.g., 71,72]. s-IgA will be measured in unstimulated saliva samples, which will be collected by means of *Salicaps* (IBL international, Hamburg, Germany).

**Table 2 pone.0263785.t002:** Biological and physiological outcome measures, number of samples, collection time point, and assessment procedure.

Stress system	Outcome measure	Number of time points	Time points	Procedure
Sympathetic Nervous System	Salivary-alpha amylase	6	Baseline, +0, +10, +20, +45, +90 minutes	Stimulated saliva samples
	Heart rate	NA	Continuously (baseline to + 90 minutes)	Electrocardiogram
Parasympathetic Nervous System	Heart rate variability (RMSSD)	NA	Continuously (baseline to + 90 minutes)	Electrocardiogram
HPA axis	Cortisol	6	Baseline, +0, +10, +20, +45, +90 minutes	Stimulated saliva samples
Immune system	CRP	3	Baseline, + 90 minutes, +24 hours	Dried Blood Spots
	IL-6	3	Baseline, + 90 minutes, +24 hours	Dried Blood Spots
	s-IgA	2	Baseline, +90 minutes	Unstimulated saliva samples

*Note*. CRP: C-reactive protein; HPA: hypothalamic-pituitary adrenal; IL-6: interleukin-6; s-IgA: secretory immunoglobulin-A; NA: not applicable; RMSSD: root mean square of successive differences.

### Assessment of sample characteristics

Demographic, anthropometric, socio-economic, lifestyle, as well as health-related variables will collected via questionnaires (e.g., age, sex, ethnicity, education, occupation, mother tongue, smoking status, diseases, medication intake). Some of these characteristics (e.g., smoking status and mother tongue) will be only collected to double-check whether inclusion criteria are fulfilled. A full item list is provided as Supplementary Material in S1 File.

### Stress perception, affect and anxiety during the experiment

During the experimental session, stress perception, anxiety, and affect as measures for the perceived (non-physiological) stress response will be assessed via the following instruments:

#### Affect

Positive and negative affect will be measured four times during the experiment by means of the Positive and Negative Affect Schedule [PANAS; 73,74]. Assessment time points will be before the task, immediately after it, 20 minutes after the task, as well as 90 minutes later.

#### State anxiety

State anxiety and depression before and immediately after the task will be measured by using the state items from the State-Trait Anxiety-Depression Inventory [STADI-S; 75].

#### Stress perception

Perceived stress will be assessed throughout the experiment at the time points of the saliva samples by means of 10-point Likert scales with the anchors “not stressed at all” and “extremely stressed”. This scale has been successfully used in previous studies from our group [e.g., 76–79]. Additionally, participants are asked about their perceived exertion as well as their level of tiredness, again on 10-point Likert scales. All three scales are provided as Supplementary Material in S2 File.

### Psychological variables

Beside demographic, anthropometric, and health -related variables (see above), the acute stress response is related with a variety of psychological variables [e.g., 55]. Therefore, psychological variables as well as lifestyle factors, which might be related with the stress responses under study, will be assessed additionally. The following standardized questionnaires or in-house developed items will be used.

#### Burnout

The Maslach Burnout Inventory [MBI; 80] will be used for assessment of burnout symptoms.

#### Coping

Coping will be assessed by means of the German 24-item version of the Coping Inventory for Stressful Situations [CISS; 81,82]. The scale assesses task-oriented, emotion-focused, as well as avoidance-oriented coping. The avoidance-oriented coping scale can be further divided into distraction coping and social-diversion coping subscales.

#### Depression

Depression will be assessed by means of the German version of the long form of the depression scale from the Center for Epidemiological Studies [CES-D; 83,84].

#### Emotion regulation

A German version of the Emotion Regulation Questionnaire [ERQ; 85,86] will be used to assess the emotion regulation dimensions reappraisal and suppression.

#### Habitual multimedia consumption

For assessment of habitual television and internet usage, items from a questionnaire for the assessment of habitual media consumption by Koch [2010; 87] will be used. Each subscale consists of 8 items that should be answered on 7-point Likert-scales. A further scale, which assesses habitual mobile phone usage, has been developed analogously based on the items by Koch [2010, 87] for habitual television and internet usage.

#### Multimedia usage

Self-developed items will be used to assess time of day at which media is used, separately for weekdays and weekends. A German version of the Media and Technology Usage and Attitudes Scale [MTUAS; 88] will be used to assess frequency of multimedia usage, social media activity, as well as attitudes towards media usage. The polychronicity (i.e., the preference for multitasking) items from the MTUAS will be left out. Polychronicity will be assessed by means of the Multitasking Preference Inventory [MPI; 57] instead.

#### Multitasking

The amount and causes of multitasking behavior in everyday life will be assessed by means of 8 self-developed items, which will be answered on 5-point Likert Scales. The items are provided as Supplementary Material in S3 File.

#### Perceived stress

Perceived stress during the last month will be assessed by means of a German translation of the 10-item version of the Perceived Stress Scale [PSS; 89,90].

#### Personality

For personality assessment, the short version of the Big Five Inventory [BFI-K; 91] will be used. This questionnaire enables assessment of the big-five personality-dimensions extraversion, neuroticism, agreeableness, conscientiousness, and openness to experience by means of 21 items.

#### Resilience

For assessment of resilience, the German 11-item resilience scale [RS-11; 92] will be used.

#### Self-efficacy

Self-efficacy will be assessed by means of a German scale for general self-efficacy [SWE; 93]. The scale includes ten items, with which self-efficacy is rated on 4-point Likert scales.

#### Social anxiety

Social anxiety will be assessed by means of the Social Interaction Anxiety Scale (SIAS) as well as the Social Phobia Scale [SPS; 94].

#### Social support

The 14-item version of the *Fragebogen zur sozialen Unterstützung* [FSozU-K14; 95] will be used to assess social support.

#### Trait anxiety

Trait anxiety and depression will assessed by means of the trait-items from the State-Trait Anxiety-Depression Inventory [STADI-T; 75]. Note that we will use the CES-D as main outcome measure for depression. However, we will leave in the depression items to not alter the psychometric properties of the STADI-T.

### Experimental setting and procedure

After providing informed and written consent, participants will be equipped with the heart rate monitors and will be familiarized with the saliva collection procedure via Salivettes (i.e., the collection of the stimulated saliva samples), and a practice saliva sample (s_0_) will be collected, which will not be used for later analyses. After this, all participants–irrespective of the actual group assignment–will conduct practice trials of the VFT and the CPT and will be informed that they will possibly have to repeat these tasks throughout the session. This will be followed by a resting period of about 20 minutes. At the end of the resting period, the first blood spot sample (DBS_1_) and the next stimulated saliva sample (s_1_) as well as the first unstimulated saliva sample (us_1_) will be collected. After this, the main task will be introduced to the participants and will then start immediately and will last about 21 minutes. Introduction of the task and the actual task will take a total of about 25 minutes. Immediately after the end of the main task, participants will provide the second saliva sample (s_2_; i.e., end of the main task +0 minutes). The subsequent stimulated saliva samples will be collected at the following time points: +10 (s_3_), +20 (s_4_), +45 (s_5_), and +90 (s_6_) minutes after the end of the main task. The second Dried Blood Spot (DBS_2_) as well as the second unstimulated saliva sample (us_2_) will also be collected at + 90 minutes post task. During the time window between the task and the last saliva and blood sample, participants will rest and will fill out questionnaires until the end of the session and will be allowed to take as many breaks as they prefer. The goal of this period is not to stress the participants while conducting a non-stressful task (i.e., filling-out the questionnaires). The timeline of the whole experiment is shown in Fig 3. The entire session will last about 3 hours. Additionally, participants will provide another blood sample (DBS_3_) 24 hours after the first one. This DBS collection will be conducted by the participants themselves at their homes and samples will be send back via mail.

**Fig 3 pone.0263785.g003:**
[figure not shown]
Timeline of the experiment. The entire session will last about 3 hours. A further Dried Blood Spot Sample (DBS_3_) will be collected 24 hours after DBS_1_ (not shown). *Note*. CPT: continuous performance task; DBS_i_: Dried Blood Spot #*i;* HRV: heart rate variability; *s*_i_: stimulated saliva sample #*i*, which will be collected by means of Salivettes; us_i_: unstimulated saliva sample #*i*; VFT: verbal-fluency task.

### Outcome measures

#### Primary outcomes

Primary outcomes will be the physiological stress measures for SNS, PNS, HPA axis, and immune system reactivity (i.e., sAA, HR, RMSSD, cortisol, CRP, s-IgA, and IL-6).

#### Secondary outcomes

Secondary outcomes will be subjective stress perception, state anxiety, and affect as well as associations between the time course of the primary outcomes with person characteristics (e.g., age and sex) and psychological variables (e.g., personality, coping style, self-efficacy, depression, anxiety, polychronicity).

### Hypotheses

#### Main hypotheses

With regard to the specificity hypothesis [45,46], we expect that pure digital stressors will trigger physiological responses of the SNS (i.e., an up-regulation), PNS (i.e., a down-regulation), as well as an activation of the immune system, but not of the HPA axis (due to the absence of a social-evaluative component). An additional activation of the HPA axis (i.e., an increase of cortisol levels) is expected for the conditions 5 and 6 (non-digital parallel dual-tasking and multitasking), in which we included a social-evaluative component by the presence of an experimenter.

Our main hypotheses, that are associated with research questions 1, 2, and 3 are:

Conditions 3 and 4 (digital work interruptions and digital parallel dual-tasking) will trigger responses of the SNS, PNS, and the immune system that are stronger than in the passive control condition 1 and the single-task control condition 2. No HPA axis response are expected for conditions 3 and 4.Conditions 5 and 6 (non-digital parallel dual-tasking and multitasking) will trigger responses of the SNS, PNS, HPA axis, and the immune system that are stronger than in the passive control condition 1 and the single-task control condition 2.

Regarding the time course of the physiological responses (if any will be found), we hypothesize fast responses of the SNS and PNS with a maximum immediately after the tasks. The HPA axis response is expected to be delayed with a maximum 20 minutes after the tasks. Slower responses are expected for the immune system with a maximum of 90 minutes after the task for IL-6 and s-IgA and 24 hours after the experimental session for CRP.

#### Secondary hypotheses

We hypothesize that conditions 3, 4, 5, and 6 will induce the perception of being stressed and that perceived stress will be stronger in these conditions than in the passive control condition 1 and the single-task control condition 2 immediately after the stressor. Furthermore, we expect to find an increase in state anxiety and in negative affect as well as a decrease in positive affect immediately after the tasks, which will be stronger than in the passive control condition 1 and the single-task control condition 2. Moreover, we expect that the physiological stress response patterns will be associated with person characteristics [e.g., age and sex; e.g., 55] and psychological variables (e.g., personality, coping style, self-efficacy, depression, anxiety, and polychronicity).

### Sample handling and laboratory analysis of blood and saliva samples

The saliva and blood samples will be analyzed in our in-house laboratory (FAU, Chair of Health Psychology, Biopsychological Laboratory, Nürnberg, Germany) by trained staff using established procedures [e.g., 71]. After collection, Salivettes and Salicaps will be stored at -30°C. On the analysis day, they will be thawed and centrifuged at 2,000 *g* at 4°C before further processing. The DBS samples will be dried for at least 8 hours at room temperature before they will be stored at -30°C. The further handling during analysis will also be conducted according to established procedures [e.g., 69,71,96]. In short, a circle with a diameter of 3.5 mm will be punched out and will be eluted overnight in phosphate buffered saline which contains 0.1% Tween 20 solution. The next morning, samples will be shaken at 300 rpm for one hour before further processing.

Concentration of sAA will be measured with an enzyme kinetic assay, as described elsewhere [e.g., 97]. For salivary cortisol, CRP, as well as s-IgA measurement, high-sensitive Enzyme-linked Immunosorbant Assays [ELISA; e.g., 98,99] will be used. For IL-6 measurement, a ProQuantum-Immunoassay-Kit (ThermoFisher Scientific, USA) will be used. For determination of absolute CRP concentrations, linear regressions will be conducted which been validated in-house. sAA, cortisol, CRP, and s-IgA analyses will be conducted in duplicates and IL-6 analyses in triplicates. Analyses will be repeated if inter- or intra- coefficients of variation will be greater than 10%.

### Heart-rate variability analysis

Several HRV parameters can be derived from the ECG signal. The most prominent one, that is calculated in the time domain of the signal, is the RMSSD which is usually used as a marker for PNS activity [68]. The RMSSD will be the main HRV measure for our analyses and will be used for main hypotheses testing. Yet, there are further HRV parameters that can be extracted from the HRV signal, e.g., in the very-low frequency (VLF), low frequency (LF), and high-frequency (HF) range, which can be derived from the power spectrum of the HRV signal [68,77]. It has been suggested that VLF power is associated with SNS activity, LF power with both SNS and PNS activity, and HF power with PNS activity [68]. However, there remains a debate whether all these components in the frequency domain reflect parts of both, SNS and PNS activity [100]. Therefore, these components will not be included in our main analyses, but additional analyses will be conducted. Another frequently used HRV parameter as a measure for sympatho-vagal balance is the ratio LF/HF [101], which will also be used for additional analyses in our study. For all these additional HRV analyses (besides the RMSSD) an adjusted alpha-level of α_adjusted =_ .001 will be applied.

### Randomization

For randomization, computer-generated randomization lists will be used, which will be stored in closed envelopes and will be handed out to the experimenters immediately prior to the experimental sessions. A team member who is not involved in data collection is responsible for randomization. Subjects are blinded and are informed that the intention of the study is the assessment of physiological responses to interaction with digital devices. Participants’ sex will be considered in the randomization process to ensure an equal sex distribution.

### Data preparation and statistical analysis

For statistical analysis, IBM SPSS Statistics (version 26 or higher for Windows) will be used. Data will be screened for outliers, and outliers which differ more than 3 standard deviations from the participants’ mean will be excluded from further analysis. Test of normality will be conducted by means of the Kolmogorov-Smirnov test. If necessary, data will be transformed (e.g., by means of the natural logarithm or square root transformation) to achieve a normality distribution.

For main hypotheses testing (research questions 1, 2, and 3), rmANOVAs will be conducted. In the analyses, the between-subjects factor ‘Condition’ (with six levels, see above) as well as the within-subjects factor ‘Time’ (with either six levels (for sAA, cortisol, and ECG measures), two for CRP and IL-6, and two for s-IgA) will be included. Three separate analyses will be conducted, one for SNS and PNS markers (i.e., sAA, HR, and RMSSD) and six measurement time points (s_1_ to s_6_), one for cortisol as the only HPA-axis marker with the same six time points, and one for the immune parameters (i.e., IL-6, CRP, and s-IgA) and two measurement time points. An additional factor ‘Measure’ (e.g., with the levels IL-6, CRP, and s-IgA for immune parameters) will be included if necessary. A Bonferroni-adjusted α-level of α_adjusted_ = 0.05/3 = 0.017 will be used for the main analyses, because three separate rmANOVAs will be conducted. The potential confounders age, sex, BMI, use of oral contraceptives and menstrual cycle phase for female participants, as well as time of day will be included in all statistical analyses as covariates.

Research question 4 (i.e., perceived stress, state anxiety, and affect) will be investigated analogously to research questions 1 to 3 by means of a further rmANOVA. The same α_adjusted_ = 0.017 as for main hypothesis testing will be used. For analysis of research question 5 (i.e., associations with person characteristics and psychological variables), nominal scaled variables (e.g., sex and education) will be included as additional factors in further rmANOVAs. For metric variables, multivariate regression analyses will be conducted in which the potential moderator variables will be included as moderator variables. For these analyses, the SPSS macro PROCESS [102] will be used. For these analyses which refer to research question 5, an adjusted α-level of α_adjusted_ = 0.001 will be used.

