### Power analysis

An a-priori power analysis has been conducted using G*Power (version 3.1.9.6). We expect to find small, but relevant effects and therefore used an effect size of *f* = 0.14 for power calculation (*f*^2^ = 0.02). We intend to achieve a power of 1 – β = 0.95 and used a Bonferroni-adjusted α-level of α_adjusted_ = 0.05/3 = 0.017 (see data preparation and statistical analysis). With these parameters a total sample size of *N* = 174 (29 per condition) is needed for an analysis of variance for repeated measurements (rmANOVA) with six measurement time points and six conditions. Based on our experience with similar studies, we expect a small drop-out rate of about 10% due to insufficient saliva or blood volumes and will, therefore, recruit additional 18 participants (3 per condition). This results in a total sample size of *N* = 192.

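### The 3 SD exclusion comes before any transformation and its reference mean is undefined: on skewed markers it removes genuine high values and then the participant; on each person's own mean it can never act on saliva or blood values

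*Protocol article*

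**What the plan says.** The steps stand in one paragraph of Data preparation and statistical analysis, in this order:

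1. Screening and exclusion: "outliers which differ more than 3 standard deviations from the participants’ mean will be excluded from further analysis".
2. "Test of normality will be conducted by means of the Kolmogorov-Smirnov test".
3. "If necessary, data will be transformed (e.g., by means of the natural logarithm or square root transformation").

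The text does not say whose mean is the reference (all participants, a condition, a time point or the individual). It does not name the scale for screening, or say whether the single value or the whole person is excluded.

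The main analysis follows in the same section: "For main hypotheses testing (research questions 1, 2, and 3), rmANOVAs will be conducted", with SPSS as the software. Under Main hypotheses, "An additional activation of the HPA axis (i.e., an increase of cortisol levels) is expected for the conditions 5 and 6", while parasympathetic activity is expected to fall. Under Power analysis, 192 participants are recruited to leave 174, the margin being for a "small drop-out rate of about 10% due to insufficient saliva or blood volumes".

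**The concern.** The plan itself foresees log or square-root transformation, so it expects some markers to be skewed. A symmetric 3 SD rule applied to right-skewed raw concentrations cuts almost only the upper tail. Where a stressor raises the marker, that tail contains the strong responders, so exclusion can depend on both outcome and condition.

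A repeated-measures ANOVA in SPSS uses complete cases, so one deleted value out of six removes the person from that analysis. Two things are at stake: a contrast pulled towards no effect in a study sized for a small effect (f = 0.14), and losses that the 10% allowance does not cover, because it is tied to sample volume alone.

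**Working it through.** **The plan's sample size.** From Power analysis: f = 0.14, alpha = 0.05/3, six conditions (k), six time points (m). Correlation 0.5 and full sphericity are assumed, since neither is stated. The noncentrality is f² × N × m / (1 − rho) = 0.0196 × 174 × 6 / 0.5 = 40.9, with (k − 1)(m − 1) = 25 and (N − k)(m − 1) = 840 degrees of freedom. Power is 0.954; at N = 168 it is 0.944. The stated 174 reproduces.

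**Reading 1: the sample mean is the reference.** For a log-normal marker with log-SD s, the upper cut-off in units of the median is t = exp(s²/2) × [1 + 3 × sqrt(exp(s²) − 1)], and the share of valid values above it is 1 − Φ(ln t / s).

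- s = 0.6: t = 1.197 × (1 + 3 × 0.658) = 3.56; ln t / s = 1.270 / 0.6 = 2.12; share 1.7%.
- s from 0.4 to 1.2: share 1.3 to 1.9%.
- Normal data, or the same data after a log: 0.13% above the upper limit, 0.27% on both sides together.

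**Consequence for participants and the contrast.** Simulation with 32 per condition and six samples each. The 3 SD rule is applied per time point with the SD pooled over conditions, a participant is dropped if any value is flagged, and the contrast is the log change from baseline to +20 minutes. The sample layout comes from the protocol; all distributional inputs are assumptions.

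*Assumption set A:* log-SD 0.5 to 1.0, within-person correlation 0.6, rise of 0.5 log units at +20 minutes in conditions 5 and 6, between-person SD of that rise 0 to 0.8.

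| Screening scale | Lost, conditions 5–6 | Lost, other conditions | Contrast (true 0.50) | Shrinkage |
|---|---|---|---|---|
| Raw | about 8–11% | about 5–8% | 0.41–0.48 | about 3–18% |
| Log | about 1–4% | about 1% | 0.47–0.50 | about 0–6% |

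The low end of the raw-scale shrinkage, about 3 to 4%, is the case in which everyone responds equally. The high end needs a response SD of 0.8 around a mean of 0.5.

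*Assumption set B:* log-SD 0.4 to 0.9, correlation 0.6, peak rise 0.3 or 0.6 spread over several samples, response SD 75% of the mean.

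- Participants with at least one flagged value: 10 to 15.5 of 192 (5.2 to 8.1%) on the raw scale, against 2 to 3 (1.2 to 1.6%) on the log scale.
- Raw scale with a response: 9.8 to 13.6% lost in conditions 5 and 6, 2.5 to 7.0% elsewhere; contrast down 6 to 13%. On the log scale it falls 1 to 4%.
- Raw scale with no response: losses equal, for example 7.0% against 6.9% at log-SD 0.6.
- Raw scale with mean and SD taken within each condition and time point (log-SD 0.6, rise 0.6): 7.0% against 6.5%; contrast 0.597 to 0.575, about −4%.

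**Power.** 192 × 0.90 = 172.8 after the volume allowance. A further 7% leaves 172.8 × 0.93 ≈ 160, with power 0.93 instead of 0.95.

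**Reading 2: each person's own mean is the reference.** Among n values the largest possible distance from their mean is (n − 1)/√n SDs:

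- n = 6 (cortisol, sAA): 5/2.449 = 2.04
- n = 3 (CRP and IL-6 as collected): 2/1.732 = 1.15
- n = 2 (s-IgA): 1/1.414 = 0.71

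None reaches 3, so no saliva or blood value could ever be excluded.

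**The case against.** A prespecified 3 SD rule is open and common, and the article lists its preparation steps without words such as first or then. Screening on the raw scale is therefore inferred from sentence order in a condensed article. That stands as a limit. It does not clear the rule, because the rule is stated, the order given is the natural one to follow, and nothing in the text points to screening after transformation.

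Stronger readings are tempting but unsupported:

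- *Exclusions fall mainly on the stress conditions.* Conditions 5 and 6 are a third of the sample (64 of 192). They supply about 37 to 50% of dropped participants under set A and about 40 to 75% under set B: disproportionate, but not reliably a majority. The imbalance needs a real rise and pooling over conditions.
- *High responders are lost for every marker.* RMSSD is expected to fall under stress, so upper-tail cuts there would hit controls or low responders.
- *On the own-mean reading the rule can never fire at all.* That holds for saliva and blood. Heart rate and RMSSD come from continuous ECG, where a within-person screen could act before values are aggregated.
- *The text excludes the whole participant.* It does not say so; the loss follows from the complete-case analysis.

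The power cost is also modest (0.93 against 0.95), and the protocol already repeats assays with a coefficient of variation above 10%.

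**Conclusion.** The point holds in limited form. In the order written and with the sample mean as reference, the rule removes genuine upper-tail values of right-skewed markers, and the planned analysis then drops those participants. For markers expected to rise, loss is disproportionate in the responding conditions and the contrast is understated, by about 3 to 18% under set A. Log-scale screening brings this to about 0 to 6%. These sizes rest on assumed spread, correlation, response and heterogeneity, none of which the documents give. The imbalance vanishes with no effect and largely disappears with screening within condition and time point. Read as each person's own mean, the rule does nothing for saliva and blood. Under neither of these two readings does it work as a sound check on those values, and the 10% allowance does not cover the losses under the first. It should be corrected, but it does not by itself undermine the trial.

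**What to change.** Amend Data preparation and statistical analysis as follows:

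1. Decide on the transformation for each marker first, then screen on the transformed scale.
2. Define the reference for screening: per measure and per time point.
3. Exclude values from the main analysis only for documented assay or recording faults, such as insufficient volume, a coefficient of variation still above 10% after repeat, or ECG artefact. Keep other flagged values.
4. Report a sensitivity analysis with the 3 SD exclusions applied, giving the number removed by condition.

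Optionally, fit a mixed model so that one missing value does not remove a participant. This is a preference; the point does not depend on it. Nor is a log required for every marker.

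The cost is plan wording and one extra sensitivity analysis. The protocol states that analysis starts only after data collection is complete, so the change can be made beforehand.
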